### Study design – Rwanda & Zambia

The study will be implemented in two sequential phases. The first is a formative phase (approximately 6 months) to establish operational requirements and assess the country-adapted ANC digital module’s functionality. The WHO digital ANC module is a tool based on WHO-guideline-derived algorithms that provides clinical decision support and person-centric management, including tracking and patient records, to assist health workers in implementing the ANC package [22]. The MoHs and country teams conducted a landscape analysis to prioritize integration of the country-adapted module to existing digital systems (e.g. DHIS 2, etc.) and customized the ANC Digital Adaptation Toolkit (DAK) [23]. During the formative phase, the WHO reference software will be adapted to create the Rwanda/Zambia ANC digital module. Qualitative methods will be employed to gauge health workers’ ability to use the module. A training package for ANC health workers [27] and related support and supervision materials will be tailored for the study. The formative component will not be carried out in health facilities that are part of the demonstration phase, but in those that share similar characteristics.

The second, demonstration phase (24 months), employs a mixed methods stepped-wedge cluster randomized design implementation trial to test the introduction of the adapted ANC package and the digital tool in selected health facilities in both clusters (Fig. 2B). Facilities will be pair-matched on the basis of factors affecting ANC enrolment, quality and facility capacity. Within each pair, a facility will be randomly chosen to start implementing first the adapted ANC package, and then the adapted ANC digital module. All selected facilities will cycle through the following steps:Baseline phase: Facilities will all begin with at least one four-month period of baseline data collection. Cluster 1 facilities will collect an additional four months of baseline data.Preparation phase for the deployment of the national package of ANC interventions: This will be a transition phase where all co-interventions, except the digital module, will be initiated. Adapted ANC package implementation phase: Health facilities will then have four months to implement the adapted ANC package.Adapted ANC package implementation and preparation for deployment of country-adapted ANC digital module: This will be a transition phase where the digital co-intervention will be initiated; the other four co-interventions will continue to be implemented.Adapted ANC package and adapted ANC digital module implementation: Facilities will deploy both the adapted ANC package and the digital tool to assist health workers in implementing the former.

### Target population

Sub-national locations (i.e. region, state, districts, province, blocks) were selected in collaboration with the MoHs. For example, in some instances, the MoH considered locations with high or low performance^1^ on maternal and child health indicators to ensure that learnings will be applicable to settings with varying level of development. Generally, health facilities need to have a minimum volume of 30 women attending ANC once per month, human resource capacity of minimum two health workers providing ANC, and physical infrastructure (e.g. separate room dedicated to ANC service delivery).

Additionally, the following exclusion criteria were applied:Health facilities where the management does not agree to participate in the study,Health workers who do not consent (qualitative components),Women who do not provide consent (all study components),Women who do not reside in the catchment area of selected healthcare facilities (Burkina Faso and India),Women who also sought ANC services from non-public health platforms, such as the private sector (Rwanda),Girls under 14 years old (Burkina Faso & India),For the cohort study:women at more than 20 weeks of gestation,women with pre-identified complications.

### Co-interventions

Country study teams are charged with deploying the co-interventions. Teams are made up of the MoH, an implementation research partner^2^ and the WHO country offices. WHO regional and headquarters offices will be involved in the overall coordination across the four countries and support in the monitoring and evaluating the study and summarizing global results. In Rwanda and Zambia, the MoH selected a local technical partner to support the digital tool adaptation; additionally, the partner that developed the WHO digital ANC module will provide support and knowledge transfer throughout the project.^3^

#### Co-intervention 1: training of selected primary healthcare staff on adapted ANC package

WHO AFRO developed training resources (including facilitator guides and presentations, etc.) for the WHO ANC recommendations. Each country team will tailor these resources for health workers who are involved in the provision of ANC services at selected health facilities. In India, Jhpiego resources were also incorporated into the training materials. Where appropriate, a Training of Trainers (ToT) model will be applied. Thereafter, ANC health workers [and in some cases, catchment area staff, such as community health workers (CHWs)] will be trained on the adapted ANC package during 3–5 day training and orientation sessions. Where applicable, existing ANC registers at selected study facilities (and catchment areas) and client cards issued to all pregnant women used for recording ANC services will be modified to capture service data according to the adapted ANC package. The training and supervision sessions (see co-intervention 2) will include capacity building of health workers on these modified recording tools.

In Burkina Faso, Rwanda and Zambia, nurses and/or midwives providing ANC service in study facilities will be trained to conduct ultrasounds (before 24 weeks of gestation). Country teams will develop a package to train primary health workers to use and interpret ultrasound machines and results. A team made up of obstetricians/gynaecologists and/or radiologist technicians will conduct the trainings, which will include an introduction to theory and a practice component. Study facilities will select at least one ANC health worker to attend. Results from the training evaluation will assist in identifying components that will require continuous support through supervision.

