**Fig. 2 Fig2:**
[figure not shown]
**A**, **B** Stepped-wedge cluster implementation designs. *Pkg* package, *ANC* antenatal care. The blue outlines refer to the nested cohort recruitment and follow up periods

Health facilities will be randomly allocated to one of four clusters. The study period of 24 months will be divided into six periods of four months each. All selected facilities will cycle through the following steps:Baseline phase: Facilities will all begin with at least one four-month period of baseline data collectionPreparation phase: This will be a transition phase where all the co-interventions will be initiated.Full implementation phase: Depending on the cluster [1–4], health facilities will implement the ANC package for a range of either one to four periods (4–16 months). Please see Fig. 2A for more information.

Implementation of the adapted ANC package will be done cluster wise from period 2 onwards, such that by period 6 all clusters would have received the intervention. Data will be collected cross-sectionally at the end of each month in each cluster.

In addition to collecting cross-sectional data in each cluster every period, two cohorts of pregnant women will be enrolled and followed through the course of their pregnancy. One cohort will not be exposed to the intervention (comparison arm). For the comparison group, pregnant women in cluster 1 and cluster 2 will be enrolled during the first three months of period 1 and followed through to the end of their pregnancy (period 3). For the intervention group, pregnant women in clusters 3 and 4 will be enrolled. To ensure comparability, for cluster 3, women will be enrolled during the first three months of period 4 and followed through to the end of their pregnancy (period 6), while for cluster 4, women will be identified and consented during the first three months of period 3 and followed through to the end of their pregnancy (period 5). Purposive sampling will be used to identify women coming for their first ANC during the first trimester. Research teams will monitor selection to ensure a balance in maternal age, parity, education level and religion.

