## Methods: evaluation

### Quantitative data (adherence to ANC package and early initiation of ANC)

The primary outcomes or indicators of interest, which will be measured to assess the impact of the adapted ANC packages, vary across each country (see Table 2). These measures are based on the WHO ANC monitoring framework [29].

**Table 2 Tab2:** Primary outcomes by country

	Burkina Faso	India	Rwanda	Zambia
Syphilis testing at first ANC contact	X	X	X	X
First ANC contact within 12 weeks	X	X	X	X
Iron and folic acid (IFA) supplementation received for 90+ days	X			
Haemoglobin (Hb) screened at first ANC contact		X	X	X
Total number of ANC contacts	X	X		
Blood pressure measurement at first ANC contact				X

X denotes which primary outcomes are being tracked in each country

Data collection for the stepped-wedge cluster randomized trial will be cross-sectional every month. Country teams will leverage existing data collection systems to gather data on primary outcomes. Specifically, teams will use ANC registers at the health facility and client cards/patient files as primary data sources. They will also collect information on cases referred to a higher level of treatment (e.g. district health hospital) for further management, where available. Secondary outcomes or indicators of interest (see Table 3) vary across each country.

**Table 3 Tab3:** Qualitative methods and stakeholder groups by country

	Burkina Faso	India	Rwanda	Zambia
Pregnant women who seek ANC at selected facilities or within the selected facilities’ catchment areas	IDIs and FGDs	IDIs	FGDs	FGDs
Husbands/partners or mothers-in-law (household decision maker) from the selected catchment areas	IDIs	IDIs	FGDs	
Selected community leaders and/or champions for maternal health	IDIs			FGDs
Community health workers rendering services within catchment area of selected health facilities	IDIs and FGDs	FGDs		
Health workers providing ANC services at selected facilities or within catchment area of the selected facilities	IDIs	FGDs	FGDs* & IDIs	FGDs* & IDIs
Health facility managers of selected facilities		IDIs	IDIs	IDIs
Government health officials/program managers responsible for maternal health programs at district/state or national level	IDIs	IDIs	IDIs	

*IDIs* in-depth interviews, *FGDs* focus group discussion

*FGDs with health workers using the digital tool during the formative phase

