### Study population and sample size

For the stepped-wedge cluster randomized trial, data will be collected cross-sectionally from facility ANC registers (modified for this study). To ensure data quality across health facilities, an orientation for improving quality or recording and reporting will be organized across all study sites at the beginning of the study.

For the nested cohort component of the study, the pregnant women who seek ANC for the first time at the selected health facilities or at public health platforms within their catchment area will be approached and invited to participate in the study. The cohort recruitment will be closely monitored and mitigation efforts, such as additional recruitment and extension of enrolment time to ensure that the sample size is not negatively impacted, will be employed.

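### Training on the registers that supply the primary outcomes is part of the crossover package, so some of a recorded rise in service items may be better recording rather than better care

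*Protocol article*

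**What the plan says.** Five statements in the protocol article matter here.

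- **What changes in the records.** Under Co-intervention 1, existing registers and client cards, where applicable, "will be modified to capture service data according to the adapted ANC package".
- **Who trains staff on them, and through what.** The same section continues: "The training and supervision sessions (see co-intervention 2) will include capacity building of health workers on these modified recording tools". Recording skills are thus taught through co-interventions 1 and 2.
- **When those co-interventions start.** For India and Burkina Faso, the preparation phase is described thus: "This will be a transition phase where all the co-interventions will be initiated". For Rwanda and Zambia: "This will be a transition phase where all co-interventions, except the digital module, will be initiated". In both designs the preparation phase follows the baseline phase, at a time set by the randomised order.
- **Where the primary outcomes come from.** Under Quantitative data, "teams will use ANC registers at the health facility and client cards/patient files as primary data sources". Data analysis of quantitative data then compares the primary parameters at baseline with those under full implementation.
- **The safeguard.** Study population and sample size describes the trial registers as modified for the study and adds that "an orientation for improving quality or recording and reporting will be organized across all study sites at the beginning of the study".

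**The concern.** A register-based service outcome is the product of two things: whether the service was given and whether it was written down. The intervention is meant to change the first. As described, it also acts on the second, through training and repeated supervision on the recording tools that begin when a facility crosses over.

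Randomising the order of crossover protects against facilities choosing when to start, and adjusting for period removes changes common to all facilities at one calendar time. Neither removes a change in recording that arrives with treatment status in each facility. A gain in completeness would be absorbed into the treatment effect and reported as better adherence. Inflating the sample by 20% for incomplete or wrong entries restores numbers; it does not correct a completeness that differs between conditions.

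**Working it through.** **1. Is recording support the same in control and intervention periods?**

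| Recording support | Control periods | From crossover |
|---|---|---|
| Orientation on recording, all sites, study start | yes | yes (already given) |
| Training on modified tools (co-intervention 1) | no | yes |
| Supervision covering those tools (co-intervention 2) | no | yes |
| Modified registers in use | probably, but no start date per facility is given | yes |

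The supervision section says visits go to all study facilities. Supervision is nevertheless a co-intervention, and the design sections start the co-interventions in the preparation phase. So the support differs by condition, although not from a zero base.

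**2. How large could the effect be?** The article states no completeness figure, so everything in this step is illustrative.

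Formula, if a blank counts as not done: recorded proportion = true proportion × completeness. With unchanged care, recorded after = recorded before × (completeness after ÷ completeness before).

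Inputs from the article: India's baseline for syphilis screening 20%, target change 15 points, data-loss inflation 20%. Assumption: the inflation is read as a starting completeness of 1/1.2 = 83%.

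- Implied true proportion: 0.20 ÷ 0.833 = 0.24.
- Completeness rising to 100%: recorded 24%, a gain of 4 points; 4/15 = 27% of the target.
- Rising only to 95%: 0.24 × 0.95 = 22.8%, a gain of 2.8 points.

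Other assumed starting values, each rising to 100%, from a recorded 20%:

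| Completeness before | Recorded after | Gain |
|---|---|---|
| 90% | 0.20/0.90 = 22.2% | 2.2 points |
| 83% | 24.0% | 4.0 points |
| 80% | 0.20/0.80 = 25.0% | 5.0 points |

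Producing the whole 15 points from recording alone would need completeness to rise by a factor of 35/20 = 1.75, for example from 50% to 87.5%.

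**3. What would that do to the test?** The article's India total reproduces: 8 facilities × 100 × 6 periods = 4,800, and 4,800 × 1.2 = 5,760. The design was rebuilt by generalised least squares for a cross-sectional stepped wedge: 4 sequences of 2 facilities, 6 periods, 100 women per facility-period, ICC 0.1, CAC 0.8, and one preparation period per sequence excluded. The design figure is not available, so this layout is taken from the text. Power for 20% to 35% is about 71% to 84% depending on the variance and ICC convention, so the stated 80% is attainable.

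The standard error of the risk difference is 0.051 to 0.059 across those conventions. For a pure recording shift b, the chance of p < 0.05 is Φ(b/SE − 1.96) + Φ(−b/SE − 1.96):

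- b = 0.04: b/SE is 0.68 to 0.78, giving 10% to 12%.
- b = 0.05: b/SE is 0.85 to 0.98, giving about 13% to 17%.

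The nominal rate is 5%. These figures carry over the assumptions of step 2.

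**The case against.** The strongest reply is that much of the remedy may already be planned. The article says that "data will be collected cross-sectionally from facility ANC registers (modified for this study", and it provides a recording orientation at every site at the start. A natural reading is that modified registers and a first round of recording support precede any crossover. This part stands: a reader might infer that control facilities record on old forms with untrained staff, or that the bias follows the crossover schedule exactly, and the article supports neither. What it does not answer is the further training and supervision on the same tools, which come only from crossover.

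The arithmetic is also open to challenge. It needs blanks to be counted as not done, which the article does not say; its data-loss allowance suggests that incomplete entries may be treated as lost. For first contact within 12 weeks, a blank gestational age is more naturally missing, so the argument is weak for that outcome and is not pressed here.

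Two stronger readings are tempting and not supported. First, because "nurses and/or midwives providing ANC service in study facilities will be trained to conduct ultrasounds (before 24 weeks of gestation"), a reader might infer that pregnancy dating shifts at crossover. No statement says a scan redates the first contact, and the direction of any shift is unknown. Second, a reader might infer that outcomes in Rwanda and Zambia move to the digital module; the article names registers and client cards or patient files as the sources.

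Finally, the cohort interviews in India and Burkina Faso cover unexposed and exposed women and ask about services received. They offer a partial cross-check, but they serve additional outcomes. The exit interviews in Rwanda and Zambia are all after implementation, so they give no control comparison.

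**Conclusion.** The point holds for the register-based service items: syphilis test, haemoglobin, blood pressure, and iron and folic acid, in the countries where each is primary. Recording support differs between control and intervention periods by design, the outcomes are read from those records, and neither randomised order nor period adjustment can separate better recording from better care. The study-start orientation makes the difference smaller without removing it.

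The size is unknown. The 4-point illustration for India, about a quarter of the 15-point target, rests on three assumptions: a starting completeness of 83%, a rise to 100%, and blanks counted as not done. It does not suggest that recording alone would plausibly produce the full target. It does show that a modest recording gain could roughly double the false-positive rate and inflate a true effect.

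**What to change.** 1. Reconcile Co-intervention 1 with Study population and sample size: state that the modified registers and client cards, and the training on them, are in place at every facility before period 1.
2. Take recording training out of the crossover package, or keep later recording support equal in control and intervention periods.
3. State that each outcome is abstracted from the same source document in all periods.
4. Report completeness of each outcome field by phase, and add a sensitivity analysis that treats blanks as missing instead of not done.

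**Cost.** Moving the register training earlier needs rescheduling and a wording change, and the completeness report uses data already abstracted. Equal recording support in every period would cost more, because control facilities would need repeated sessions. One downside: registers built around the adapted package may prompt some of its care in control periods and slightly dilute the contrast. That is likely a small price for an adherence effect that can be interpreted.

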#### Co-intervention 2: supervision needs to support staff and ensure fidelity of deployment of adapted ANC package

Country teams (possibly including relevant district and/or national focal persons) will conduct structured supervision visits to all study facilities. Where applicable, mentoring of facility staff will also be carried out during this process. Standardized tools will be employed during supervision visits. These visits will include support and mentoring of ultrasound trainees (except in Indian states) and on the use of the ANC digital tool (Rwanda and Zambia only). For the latter, the local technology partner and country team will ensure that the health workers using the digital tool are adequately supported.

#### Co-intervention 3: availability of supplies for country/state-level ANC package

Country teams will conduct facility assessments at each site, once every four months, to monitor the availability of supplies (drugs, supplements, testing kits, equipment, etc.) which are required for implementing the adapted ANC package. They will use a standard facility assessment checklist for carrying out the assessments. If needed, the country team will reach out to the respective local-level authorities to ensure that supplies are replenished in time and there are no stockouts. Additionally, where appropriate, the implementation research partner will provide supplies (from a buffer stock) to ensure the ANC package can be implemented.

#### Co-intervention 4: community mobilization on country/state-level ANC package

Existing community mobilization activities will be harnessed to generate awareness on the adapted ANC package among pregnant women and their communities. Depending on the setting, this will include CHWs and/or community leaders and/or maternal health groups or committees serving in the study sites’ catchment areas. A scoping review of community mobilization activities for ANC uptake and early ANC was conducted to inform and support this process [28]. Activities to distribute messaging regarding the adapted ANC package may include conducting regular community-level sensitization meetings, home visits to pregnant women, facilitation of educational talks during maternal support groups, etc. Country teams will use information, education and communication materials such as flip charts, posters, etc. (as applicable) for conducting these activities. Where CHWs are involved, country teams may include them in their trainings and supervision visits to the study sites.

#### Co-intervention 5: (Rwanda & Zambia only) training of select health centre staff on the country-adapted ANC digital module

To train health workers in the use of the country-adapted ANC digital module, a generic training resource package (including facilitator guides and presentations, etc.) has been developed and adapted for use in each country. ANC health workers will use smartphones for service provision. Country teams will apply a ToT model where appropriate.

